#### Multivariable models to predict response to treatment

In additional analyses, multivariable logistic regression will be employed to assess patient characteristics associated with an increased likelihood of response to treatment, defined as at least 50% reduction in the number of UI episodes at one year. The logistic model will include, as independent variables, (a) the binary indicator of the trial arm, (b) the pre-intervention number of UI episodes, and (c) all previously listed covariates: age, BMI, general health status, level of physical activity, medical history and medications, parity and obstetrical history as well as type and duration of UI and current pad use. Independent, statistically significant predictors of response will be identified by *p* < 0.05 for the respective multivariable model-based two-tailed 1-df Wald test and their effects will be summarized by adjusted odds ratios with 95% CIs.

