### Onsite eligibility evaluation (1 h)

Women are scheduled for onsite evaluations with a physiotherapist if they report at least three UI episodes on the seven-day bladder diary. After signing the consent form, the Mini-Mental State Examination [48] questionnaire is completed (excludes women with cognitive impairment) and a vaginal exam is conducted to identify any perineal pain or prolapse likely to interfere with either the evaluation or the intervention. Those not eligible for the present study are referred back to their healthcare provider. Eligible participants complete the evaluation and are randomized to either individualized or group PFMT.

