### Outcome measures and moderators/confounders

#### Primary outcome measure

The primary outcome measure is the mean percent reduction in the total number of UI episodes one year post randomization, as measured by a seven-day bladder diary [28]. For example, a participant experiencing four leaks per week pre intervention and two leaks per week at the one-year follow-up would be considered to have had a 50% reduction in leakage episodes. The number of leaks (as measured by the seven-day diary) is considered one of the most reliable measures of success for incontinence treatment and has been widely used in this type of research [16, 28, 44, 47, 51]. Moreover, the reduction in the number of daily leaks, expressed as a percentage, is information that can be easily understood by participants in pre-treatment counseling. As a measurement tool, the seven-day diary has a high compliance rate and good reproducibility [28, 56].

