To err on the conservative side, we relied on the “standard” 95% CI, which corresponds to a stringent one-tailed type I error rate of α = 0.025 (2α = 1–0.95 = 0.05). Similar to other recent non-Inferiority trials (e.g. [70, 71]) and CONSORT guidelines [68], for the purpose of sample size calculation, we assume that the true difference between the mean reductions (%) achieved by the two interventions will be zero (i.e. that they are equally effective). Note that this assumption of equivalence of the two interventions being compared in our trial is consistent with both (a) clinical expectations and (b) (limited) published evidence concerning young and middle-aged UI women [72–74]. Finally, both published trials, which evaluated similar interventions in older women, reported within-group standard deviations (SD) of the individual % reduction scores of about 27% [44, 75]. Accordingly, we assumed SD = 27% in our calculations.

Under the above assumptions, we estimated the sample size needed to ensure high (90%) power to demonstrate the non-inferiority of the group-based intervention (assuming, as mentioned above, that the true difference is 0%). Thus, we calculated N, for which the probability that the upper boundary of the two-tailed 95% CI for the difference in the mean relative reduction (Individual – Group) excludes the “upper threshold of non-inferiority” (10% difference), will reach at least 90%. The sample size calculations were performed using the program in the PASS software package, designed specifically for power/sample size estimation for non-inferiority trials [76]. Under the assumptions outlined above, we will need 155 participants per group, for a total of 310 individuals. We also need to account for possible losses to follow-up, as we expect a 15% attrition rate by the end of the one year, based on both our pilot data and similar published trials [16, 17, 22, 51]. Thus, we will recruit an additional 54 participants per group, increasing the total number of participants to 364 (364*(1–0.15) = 310).

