Analyses for the primary outcome at one year (and secondary outcomes): The primary analysis will test our main hypothesis that group-based classes are not inferior to individualized treatment with respect to the primary outcome of relative (%) reduction in the number of leakages at one year post randomization. (For all outcomes, the analyses outlined below will be repeated using data on post-intervention assessment.) As recommended for non-inferiority trials, the hypothesis of non-inferiority will be accepted if, and only if, the upper bound of the two-tailed (1-2α) 95% CI (corresponding to a conservative Type I error of 0.025 for the one-tailed independent-group t-test) for the mean difference (in % reduction) excludes the non-inferiority threshold [68], set at 10% difference. This basic analysis will be extended to multivariable analyses. Specifically, two multivariable linear models, of increasing complexity, will be used to adjust the estimated difference between the % reduction at one year in the two groups for, respectively, (1) only the two stratification variables (center and type of UI), as well as the baseline number of UI episodes (to account for regression to the mean phenomenon); and (2) (if necessary) in addition to variables in model (1): any variable, for which a clinically important imbalance between the two arms is revealed by descriptive analyses (see above). In both models, the two-way interactions between the trial arm and (a) center and (b) UI type, will be tested using 1-df model-based F-tests to verify if the difference between the effects of the two interventions depend on either of those stratification variables. In the case of a statistically significant interaction (*p* < 0.05 for the F-test), the intervention effects will be estimated and tested separately in the respective subgroups [79]. The results of multivariable linear regression analyses will be summarized in terms of adjusted mean difference between the outcomes in the two trial arms, together with the 95% model-based CIs. In sensitivity analyses for primary and secondary outcomes at one year, ITT analyses will be conducted, using the same statistical methods.

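### The response-prediction model tests the baseline leak count as a predictor of a response defined from that same count, so diary noise will often make it look like a predictor of who responds to treatment

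*Protocol article*

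**What the plan says.** All references are to the protocol article.

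- **Multivariable models to predict response to treatment.** The purpose is exploratory: "In additional analyses, multivariable logistic regression will be employed to assess patient characteristics" that go with response. Response is "defined as at least 50% reduction in the number of UI episodes at one year". The model contains "a) the binary indicator of the trial arm, (b) the pre-intervention number of UI episodes, and (c) all previously listed covariates"; current pad use and type and duration of UI are among those covariates. A term counts as an independent predictor if p is "< 0.05 for the respective multivariable model-based two-tailed 1-df Wald test". The section exempts no term from this rule and gives no caveat on the baseline count.
- **Data analysis.** The linear models for the primary outcome adjust for the stratification variables "as well as the baseline number of UI episodes (to account for regression to the mean phenomenon").
- **Onsite eligibility evaluation.** Women go on to the onsite visit "if they report at least three UI episodes on the seven-day bladder diary".
- **Primary outcome measure.** The article says that "the seven-day diary has a high compliance rate and good reproducibility", but gives no coefficient.
- **Sample size calculation.** Two published trials "reported within-group standard deviations (SD) of the individual % reduction scores of about 27" percent.

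**The concern.** The section asks which women respond to pelvic floor muscle training. For the baseline count, the Wald test asks something else: whether one week's observed count is unrelated to a ratio that has this count in its denominator. If diaries vary from week to week, a woman whose baseline week was high by chance will tend to show a large fall later, whatever treatment did for her. The entry rule of at least three episodes adds selection on the same diary.

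The protocol knows this mechanism. It names regression to the mean in the Data analysis section and adjusts the linear models for it. In the response model the same variable is subject to a rule that turns its significance into a finding. Applied as written, the rule could lead to a report that women with more leaks respond better to training when the data show only diary noise. The Discussion expects the results to matter to clinicians and decision-makers.

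**Working it through.** **1. The mechanism, on the protocol's own example.** The Primary outcome section describes a woman with four leaks per week before treatment and two at one year. Keep her one-year count at 2 and let only the baseline week vary:

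- baseline 3: (3 − 2)/3 = 33%, non-responder
- baseline 4: (4 − 2)/4 = 50%, responder
- baseline 5: (5 − 2)/5 = 60%, responder

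All three baselines meet the entry threshold. Nothing about treatment differs, yet the higher count is the responder.

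**2. Number of women available.** The stated sample size reproduces. By the normal approximation, n = 2 × (27/10)² × (1.960 + 1.282)² ≈ 153.2, so 154 per arm. Noncentral-t power is 0.8997 at 154 and 0.9015 at 155, which gives the protocol's 155 per arm, or 310 analysable. For attrition, 310/0.85 = 364.7 against 364 stated. The response model was therefore simulated with about 310 women.

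**3. Simulation under no true predictor.** True percent reduction was independent of severity and of every covariate. The observed counts were:

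- baseline ~ Poisson(λ × g₀), kept if at least 3
- one year ~ Poisson(λ × (1 − r) × g₁)
- response = 1 if the one-year count ≤ 0.5 × baseline count

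Here λ is the woman's true weekly rate, r her true reduction, and g₀ and g₁ are independent gamma multipliers with mean 1 (or fixed at 1 for Poisson noise only). The logistic model contained arm, baseline count, a covariate unrelated to severity and a covariate correlated 0.4 with true severity. There were 1,000 runs per scenario.

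Assumed, because the documents do not give them: gamma-distributed λ with mean 14 or 20, mean true reduction 40% to 80%, the size of the diary noise, and that the entry diary is also the baseline diary.

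**4. Results: rejection at nominal 5%.**

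| Term | No diary noise | SD of % reduction about 22–34% (test-retest 0.59–0.93) | SD 35–86% |
|---|---|---|---|
| Baseline count | 4–6% | 33–97% | 5–10% with Poisson noise only; 27–87% with overdispersed noise |
| Covariate correlated 0.4 with severity | – | 6–25% | up to 32% |

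Across the scenarios the arm test rejected in 3–6% and the unrelated covariate in 3–7%. Near the protocol's SD, the spurious odds ratio for baseline was about 1.4 to 3.6 per SD of the count.

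Four examples with the 0.4-correlated covariate in the model:

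| Diary noise | Test-retest | SD of % reduction | Baseline count rejects |
|---|---|---|---|
| Poisson only | 0.92 | 24% | 37% |
| Poisson only, mean λ = 20 | 0.93 | 25% | 49% |
| Gamma, k = 10 | 0.77 | 28% | 88% |
| Gamma, k = 4 | 0.61 | 33% | 94% |

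A separate run at SD 28–30% and test-retest about 0.9 gave 45–68%, so the inflation does not need extreme noise.

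**5. What drives the range.** The scenarios near 27% gave true reduction an SD of only 5 to 15 percentage points, so diary noise supplied much of the rest. Where true reduction varies more between women and noise is only Poisson, the rate is lower. Another simulation with mean reduction 65% gave 13–19% with Poisson noise only; SDs of percent reduction across that simulation were 33–55%. The documents do not say how the 27% divides.

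**6. Spill-over to other covariates.** With the noisy count held fixed, a woman with higher true severity is one whose baseline week was low by chance, so a severity-related covariate is pushed in the opposite direction. At a correlation of 0.3 with log severity, such a covariate rejected in about 6–20%. Without the count in the model, a covariate correlated 0.4 rejected in 4–8% near the protocol's SD, and up to 13% in wider-SD scenarios.

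**The case against.** The strongest reply is that the model predicts response as defined. The observed count is known before treatment and does predict that outcome, so the association is real, and adjusting for baseline is standard. The analysis is labelled additional, and interpretive caveats are often left to a fuller document. Much of this stands: the count belongs in the model as an adjuster, and its coefficient misleads only if read as showing who benefits. But the section's question is response to treatment, and its written rule promotes any significant term to a predictor. That is a stated rule, not an omitted detail.

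A reader might also infer more than the documents support:

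- **That all Wald tests in this model are invalid.** They are not. Arm and covariates unrelated to severity stay near 5%.
- **That sharing the count is itself the fault.** Without diary noise the baseline test holds its level. Noise is needed, and the article calls reproducibility good, which reduces the problem but need not remove it.
- **That pad use, UI type and UI duration are all badly biased.** Rejection rates of 19–84% arise only for a covariate correlated about 0.8 with log severity. The documents give no such correlation for any listed covariate. Current pad use is a plausible case; type and duration are open.
- **That the count should simply be dropped.** That loses the adjustment the protocol itself values and leaves some residual inflation.

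**Conclusion.** The point holds in a limited form. Under the rule as written, the baseline leak count will often be named a predictor of response when true percent reduction is unrelated to severity: about 33–97% of trials in the scenarios examined near the protocol's SD of 27%, and from 5–10% up to 87% in wider-SD scenarios, against a nominal 5%. Covariates correlated 0.3 to 0.4 with severity are inflated to about 6–32%.

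The direction is firm once diaries vary from week to week. The size is not, because it rests on assumed severity, assumed diary noise and an assumed split between noise and true variation in response. The consequence is confined to an additional analysis. A reader might take this as a challenge to the trial's main result, but the non-inferiority test and the sample size do not use this model.

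**What to change.** In the section on predicting response to treatment:

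1. State that the pre-intervention count is included only to adjust for regression to the mean, as in the Data analysis section.
2. Exclude it from the p < 0.05 rule for naming predictors, and state that its odds ratio is not read as showing who responds to treatment.
3. Add a sensitivity model that replaces the count with a baseline severity measure that does not enter the response definition and is already collected: the 24-h pad test or the ICIQ-UI short form. Report a severity-related covariate as a predictor only if it also holds in that model.

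The cost is a few sentences and one extra exploratory model on data already in hand. The trial gives up reporting baseline leak count as a predictor of response. The sensitivity model is a check, not a perfect correction, since some residual inflation remains when the count is left out.

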## Discussion

Considering demographic projections, human resources, and health system constraints, there is a pressing need to scale up evidence on the long-term benefits of low-cost interventions in urinary incontinent aging women and thereby improve clinical, functional, and social outcomes of this highly prevalent condition in this subpopulation. This GROUP trial, the first adequately powered RCT, seeks to study the non-inferiority of group PFMT in comparison to individual one-on-one PFMT in aging women with UI. If group-based PFMT classes prove to be equally effective, as well as more cost-effective, compared to individual one-on-one PFMT sessions, this trial could have a positive impact on the accessibility of continence care for aging women in Canada.

The results of this RCT will be relevant to clinicians and clinical decision-makers as well as to administrative stakeholders. It will have implications for the organization and the administration of continence care services. Ultimately, the results may influence the cost of treatment per individual, the accessibility of conservative management, and the use of more invasive UI interventions such as medication and surgery in older UI women.

### Dissemination of study finding

The results of this study will be disseminated through national and international scientific and professional conferences, in addition to undergraduate and postgraduate courses in PFM rehabilitation for physiotherapists.

## Trial status

This trial is actively recruiting participants (353/364). The trial is ongoing and has a planned duration of five years, with recruitment running from September 2012 to March 2017.

## Abbreviations

DBICI: Dowell–Bryant Incontinence Cost Index
ICIQ modules: International Consultation on Incontinence questionnaire modules
ICIQ-FLUTSex: ICIQ-Female Lower Urinary Tract Symptoms sex
ICIQ-LUTSquol: ICIQ-Lower Urinary Tract Symptoms quality of life
ICIQ-N: ICIQ-Nocturia
ICIQ-UI short form: ICIQ-Urinary Incontinence short form
ICIQ-VS: ICIQ-Vaginal Symptoms
PFM: Pelvic floor muscle
PFMT: Pelvic floor muscle training
RCT: Randomized controlled trial
UI: Urinary incontinence
US: Ultrasound
